## Abstract

**Background:**

Amblyopia (lazy eye) affects the vision of approximately 2% of all children. Traditional treatment consists of wearing a patch over their ‘good’ eye for a number of hours daily, over several months. This treatment is unpopular and compliance is often low. Therefore results can be poor. A novel binocular treatment which uses 3D technology to present specially developed computer games and video footage (I-BiT™) has been studied in a small group of patients and has shown positive results over a short period of time. The system is therefore now being examined in a randomised clinical trial.

**Methods/design:**

Seventy-five patients aged between 4 and 8 years with a diagnosis of amblyopia will be randomised to one of three treatments with a ratio of 1:1:1 - I-BiT™ game, non-I-BiT™ game, and I-BiT™ DVD. They will be treated for 30 minutes once weekly for 6 weeks. Their visual acuity will be assessed independently at baseline, mid-treatment (week 3), at the end of treatment (week 6) and 4 weeks after completing treatment (week 10). The primary endpoint will be the change in visual acuity from baseline to the end of treatment. Secondary endpoints will be additional visual acuity measures, patient acceptability, compliance and the incidence of adverse events.

**Discussion:**

This is the first randomised controlled trial using the I-BiT™ system. The results will determine if the I-BiT™ system is effective in the treatment of amblyopia and will also determine the optimal treatment for future development.

**Trial registration:**

ClinicalTrials.gov identifier: NCT01702727

## Background

Amblyopia occurs when normal visual experience is disrupted during the critical periods for visual development. It most commonly presents in association with strabismus, anisometropia or both. Several forms of treatment for amblyopia exist but occlusion treatment is the gold standard and involves covering the good eye with a patch for a prescribed period of time each day [1]. The length of patching treatment varies and ranges from 10 minutes daily to all waking hours [2]. The child must wear the patch at home or school and typically, 120 hours of patching treatment results in 1 LogMAR line of improvement in visual acuity [3]. Treatment is prolonged and this contributes to poor compliance. Many children refuse to wear their patch for the prescribed time and this is a major cause of failure of treatment. Many children feel they are stigmatised by the wearing of a patch. Dixon-Woods *et al*. [4] reported patching caused distress and other negative outcomes such as relationship strain. In extreme cases, non-compliance with patching can result in a child having a costly admission to hospital to have supervised patching treatment. In addition, wearing a patch prevents both eyes being used at the same time which eliminates any advantage of binocularity (using the two eyes together as a pair).

Other forms of amblyopia treatment are used such as atropine eye drops and optical penalisation. These are usually chosen as secondary treatments if patching fails, and act by reducing the vision of the good eye in order that the child uses the amblyopic eye to see. All the existing traditional treatments rely on penalisation of the good eye with either a patch, eye drops or through the use of lenses (optical penalisation).

As an alternative to this treatment, we have developed a virtual reality-based system to treat amblyopia where children play special video games and watch DVDs. This interactive binocular treatment system (I-BiT™) uses specially configured software to preferentially stimulate the amblyopic eye without compromising the vision in the good eye. The treatment activity is designed to be enjoyable and, importantly, the child does not have to suffer the unpleasant experience of having their vision limited by the sole use of their amblyopic eye (as they do with patching). The treatment has so far been delivered in the hospital eye clinic but the I-BiT system has the potential to be further developed for use in the home environment in the future.

Previous pilot studies [5] have shown the I-BiT™ system to be highly effective in improving the visual acuity in amblyopic patients. Since we first began our studies, 3D technology has improved and we have recently conducted a pilot study to assess delivery of I-BiT™ treatment using the latest generation of shutter glasses technology [6]. This study showed that all patients who completed their planned treatment (9 of the 10 patients) showed an improvement in visual acuity. These improvements ranged from 0.025 to 0.45 LogMAR units with a mean of 0.18 (sd 0.143) and a median of 0.175.

While the study did have limitations (it was uncontrolled, unblinded and the sample size was small) the results were promising and warranted further investigation in a randomised controlled study. This study will aim to compare the effect of the I-BiT™ game with the I-BiT™ DVD and also to compare the effect of the I-BiT™ game with a control in which the patient plays the game without the amblyopic eye being preferentially stimulated.

## Methods/design

### Objectives of the study

The primary objective of the study is to investigate whether there is any difference in visual acuity in patients treated with I-BiT™ *versus* non-I-BiT™ and also if there is any difference between the two treatment stimuli (interactive game *versus* DVD). Therefore two comparisons will be made: differentiation of the type of I-BiT™ treatment and differentiation of I-BiT™ from non-I-BiT™.

Secondary objectives include examining visual acuity at additional time points (mid-treatment and 4 weeks after treatment has stopped), investigating the proportion of patients showing a response to treatment (a change from baseline of 0.125 or more [7]), the proportion of change in visual acuity, the change in binocular function, the acceptability of the treatment to the patient, compliance with treatment, and the safety profile of the treatment.

### I-BiT™ shutter glasses system

The I-BiT™ system hardware consists of a desktop PC with two monitors, one for the clinician and one for the patient. As with all previous I-BiT™ system prototypes, the clinician monitor is used to control the treatment the patient receives and the patient monitor displays the visual stimuli. The system uses 3D shutter glasses and their corresponding infra-red emitter. The patient monitor is a flat-screen 18-inch 3D monitor with a refresh rate of 120 Hz as required for use with the shutter glasses. The shutter glasses lenses lighten and darken in synchrony with the monitor but faster than the user can perceive. The patient sits on a comfortable gaming beanbag for the duration of their treatment.

This I-BiT™ system relies on the same principle as previous prototypes [8]. Images are presented to both eyes but parts of the image are presented only to the amblyopic eye. The visual scene with the I-BiT™ system is not presented stereoscopically. Instead the 3D technology is used to present a distinct but visually related image to each eye allowing the perception of a dynamic, two-dimensional visual scene. The I-BiT™ system can display video footage and interactive games. A gaming control pad is used for the games. The games have been specifically developed to appeal to children aged 8 years and under. The visual stimuli presented in the current study are described below.

### Video stimulus

The principle employed is that the image is divided into two zones. There is an outer ‘border’ termed a locking stimulus which is presented to both eyes while the inner part of the screen presents the video footage to the amblyopic eye. Images within the border can be selectively shown to either eye to act as a control to ensure binocular viewing. The DVD transparency settings for the non-amblyopic eye can be adjusted for those with dense suppression if required. This is to encourage continued viewing and fixation with the amblyopic eye. To increase compliance the I-BiT system has a built in DVD player and this allows children to watch a DVD of their own choice.

### Game stimulus

An interactive game called ‘Nux’ will be used to provide the game-play. In Nux, a player moves through a colourful two-dimensional space-like environment. Points are rewarded for collecting coins and shooting enemies and deducted for colliding with enemies and obstacles (for example, asteroids). Through the I-BiT™ system, the player and the background are shown to both eyes but the obstacles, enemies and coins are shown only to the amblyopic eye. Therefore, in order for the child to play the game successfully, they must use their amblyopic eye. If the patient is unable to play due to dense suppression or severely reduced visual acuity in their amblyopic eye then the settings can be adjusted so that a proportion of the objects (coins and so on.) are seen by the non-amblyopic eye. In the non-I-BiT game version (control arm) both eyes receive identical stimulation.

### Design

The study is a randomised parallel group, double-masked design. Eligible patients are randomised to one of three treatments:

• I-BiT™ game

• Non-I-BiT™ game

• I-BiT™ DVD

They will receive their randomised treatment weekly for 6 weeks, for a 30-minute period (Figure 1). Their visual acuity will be assessed pre-treatment, after three treatments, after six treatments and 4 weeks after their final treatment. Visual acuity will be assessed by an independent assessor who has no knowledge of the randomised treatment. The orthoptist treating the patient will have no knowledge of the results of the patient’s visual acuity assessments. The study is therefore masked.

**Figure 1 F1:**
[figure not shown]
Outline of study procedures.

Two comparisons are to be made: I-BiT™ game *vs.* non-I-BiT™ game and I-BiT™ game *vs.* I-BiT™ DVD.

### Eligibility criteria

#### Inclusion criteria

• Diagnosis of anisometropic, strabismic or mixed amblyopia as made by an orthoptist (difference of 2 LogMAR units or more using a LogMAR crowded test)

• Male or female

• Aged 4 to 8 years inclusive

• Participant’s parent or guardian is willing and able to give informed consent for participation in the study

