### Week 3 (mid-treatment)

Uniocular assessment of visual acuity with a LogMAR test (aided with glasses if applicable) after third treatment.

If at this visit, visual acuity in the amblyopic eye has regressed by 0.1 LogMAR units or more, then the participants should be withdrawn from the study.

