### Outcomes

#### Primary outcome

The primary variable is visual acuity. Visual acuity is measured in units of 0.025 (which equates to one letter). Improvement in visual acuity is measured as an increase of 0.025 LogMAR units.

The primary endpoint is the change from baseline to the end of treatment (6 weeks) in visual acuity.

The secondary endpoints are:

• Change in visual acuity from baseline to the end of the follow-up period (week 10)

• Change in visual acuity from baseline to week 3

• Proportion of patients showing a clinically important change in visual acuity (a change of 0.125 LogMAR units or more) at weeks 3, 6 and 10

• Proportion of change in visual acuity [9] at weeks 3, 6 and 10

• Change in binocular functions from baseline to week 6/week 10

• Proportion of patients reporting outcomes in each item of the patient satisfaction questionnaire

• Percentage compliance with treatment

• Proportion and type of adverse event

Proportion of change is measured as follows:

$$\mathrm{Proportion}\;\mathrm{of}\;\mathrm{change}=VA_{\mathrm{as}}-VA_{\mathrm{ae}}/VA_{\mathrm{as}}-VA_{\mathrm{fe}}$$

VA_as_ is vision of amblyopic eye at baseline, VA_ae_ is vision of amblyopic eye at the ‘end of treatment’ and VA_fe_ is the vision of the non-amblyopic eye at the’ end of treatment’ [9]. ‘End of treatment’ is the time point the change is being measured up to, that is, weeks 3, 6 and 10.

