### Sample size

Assuming a standard deviation (SD) of 0.25 [8], 25 patients per arm would be required to detect a minimum difference of 0.2 LogMAR units at the 5% significance level (two-sided) with 80% power. Therefore a total of 75 patients would be required.

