## Trial status

As of 6 November 2012, 21 patients have been randomised. Recruitment will continue until 75 patients are randomised.

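### The entry criterion of 2 LogMAR units does not fit the LogMAR scale used in the rest of the protocol, and the article does not settle which value is meant

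*Protocol article*

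**What the plan says.** The Inclusion criteria accept anisometropic, strabismic or mixed amblyopia diagnosed by an orthoptist and add a numerical threshold in parentheses: "difference of 2 LogMAR units or more using a LogMAR crowded test". This is the only numerical acuity criterion for entry. The sentence does not say between what the difference is taken; I read it as between the two eyes.

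The article uses the same scale in several other places:

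- Primary outcome: "Visual acuity is measured in units of 0.025 (which equates to one letter". A clinically important change is "a change of 0.125 LogMAR units or more".
- Week 3 (mid-treatment): the withdrawal rule applies if "visual acuity in the amblyopic eye has regressed by 0.1 LogMAR units or more".
- Sample size: 25 per arm to "detect a minimum difference of 0.2 LogMAR units", with an SD of 0.25.
- Background, on the pilot study: "These improvements ranged from 0.025 to 0.45 LogMAR units with a mean of 0.18 (sd 0.143) and a median of 0.175".
- Background, on patching: "120 hours of patching treatment results in 1 LogMAR line of improvement in visual acuity". Here the word is line, not unit.

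No section gives LogMAR units a different meaning for eligibility. Trial status reports that recruitment was under way: "As of 6 November 2012, 21 patients have been randomised".

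**The concern.** A whole LogMAR unit is a large quantity on the scale that this protocol defines, and the entry criterion asks for two. Elsewhere the article counts in steps of 0.025, and no other figure that it gives in LogMAR units exceeds 0.45. The likely explanation is a slip in the unit, but the text leaves more than one way to repair it.

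The criterion decides who is in the trial. Eligibility must be checked before randomisation, so each site needs a single threshold, and readers of the results need to know which children the estimate applies to. If sites resolve the wording for themselves, the threshold in use is undocumented and may differ between assessors.

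**Working it through.** **1. The plan's own sample size.** Inputs from Sample size: difference 0.2, SD 0.25, two-sided 5%, power 80%. The normal approximation gives n = 2 × (1.960 + 0.842)² × 0.25² / 0.2² = 2 × 7.85 × 1.5625 = 24.5, so 25 per arm and 75 in total. The stated figure is reproduced (power at 25 per arm is 0.807; a t-test version gives 0.791). The eligibility threshold does not enter this formula, so correcting it leaves the sample size as it is.

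**2. Conversion of the threshold.** With 0.025 LogMAR per letter (Primary outcome), 2 / 0.025 = 80 letters.

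**3. How the article uses the unit elsewhere.** The other values given in LogMAR units are 0.025 (one letter), 0.1 (week 3 rule), 0.125 (clinically important change), 0.2 (detectable difference) and 0.025 to 0.45 (pilot gains). The largest is 0.45, and 2 / 0.45 = 4.4. These are changes or differences in change, not entry deficits, so the ratio shows how the unit is used and proves nothing by itself.

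A closer comparison uses the proportion-of-change endpoint, which divides the gain by the deficit against the other eye. For a child exactly at a literal threshold of 2.0, with the other eye unchanged, a gain of 0.2 gives 0.2 / 2.0 = 10%, and the mean pilot gain gives 0.18 / 2.0 = 9%. Every child with a larger deficit would score lower for the same gain.

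**4. Readings that the wording permits.**

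| Reading | LogMAR | Letters at 0.025 | Rests on |
|---|---|---|---|
| Literal | 2.0 | 80 | the text as written |
| Two lines | 0.2 | 8 | 0.1 per line (4 letters), not stated in the article |
| Two measurement steps | 0.05 | 2 | reading unit as the 0.025 step under Primary outcome |

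The literal value is 2.0 / 0.2 = 10 times the second reading and 2.0 / 0.05 = 40 times the third.

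**5. Who would qualify under the literal reading (illustration only).** The article gives no distribution of the between-eye difference. Assume a normal distribution with mean m from 0.3 to 1.0 and SD s from 0.25 to 0.5. The share at or above 2.0 is 1 − Φ((2 − m)/s).

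- m = 0.3, s = 0.25: z = 6.8, share about 5 × 10⁻¹².
- m = 0.5, s = 0.5: z = 3.0, share 0.13%.
- m = 1.0, s = 0.5 (the most favourable corner): z = 2.0, share 2.3%.

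Under the same assumptions the share at or above 0.2 runs from about 58% (m = 0.3, s = 0.5) to 99.9% (m = 1.0, s = 0.25).

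Even in the most favourable corner, 21 literally eligible children would imply about 21 / 0.02275 ≈ 920 assessed. The article gives no screening count to set against this.

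**The case against.** The strongest reply is that this is a journal article condensing a fuller protocol that is not at hand. The slip may exist only in the article, and the operative criterion may be worded correctly. Entry also depends on an orthoptist's diagnosis, with the figure only in parentheses. This stands as a limit on what can be claimed. It does not remove the point, because the article has not left something out; it states a figure that conflicts with its own scale.

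A second reply is that a deficit at entry can properly be much larger than a treatment effect. It would therefore be wrong to call the threshold an error because it is ten times the difference the trial is powered for. This also stands. The case rests on the size of 80 letters, on the consistent use of the unit elsewhere, and on line being a separate term.

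Third, the effect on the analysis is small. The primary analysis is by intention to treat, the sample size does not depend on the threshold, and the per-protocol analysis is optional and supportive. All of this is correct.

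A reader might go further and infer that every child enrolled so far is a protocol deviation. The article does not support that. The 21 randomisations suggest that a threshold other than the literal one is being applied, and nothing here shows what any child was assessed against. Nor does any section tie the per-protocol set to this criterion, so it cannot be said that the set rests on an undefined rule.

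**Conclusion.** The criterion is wrong as written, or at least cannot be reconciled with the scale that the same article defines: 2 LogMAR units is 80 letters. This part needs no assumption beyond the article's own 0.025 per letter. It is an inconsistency of units in an eligibility rule, not an error in any calculation.

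Two stronger conclusions are tempting and go beyond the text. One is that the value is exactly ten times too large. That requires two lines to be meant and a line to be 0.1 LogMAR; the article states neither, and its wording also admits 0.05. The other is that the literal rule is shown to exclude practically every child. It probably would exclude most or nearly all of them, but the figure of at most about 2% depends on the assumed normal distribution, with mean 0.3 to 1.0 and SD 0.25 to 0.5.

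The point still deserves correction because this threshold defines the trial population.

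**What to change.** The sponsor should reconcile the inclusion criterion with the Background, Primary outcome and Sample size sections. It should restate the criterion as a difference between the two eyes, as a LogMAR value on the 0.025-per-letter scale, in the unit actually applied at the sites. If lines are used, the LogMAR value of a line should be given. Which value applies is for the sponsor to confirm; this review does not propose one.

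The baseline acuity records of the children already randomised should then be checked against the confirmed threshold. If eligibility enters the per-protocol definition, the same figure should be used there.

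The cost is a one-line correction and a review of existing records: 21 children at the reported date, with 75 − 21 = 54 still to be randomised. No change to the sample size or to the primary analysis follows.

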### Exclusion criteria

The participant may not enter the study if any of the following apply:

• Stimulus deprivation amblyopia

• Organic lesions of the eye preventing the establishment of good vision (for example, media opacities, abnormalities in the fundus or optic nerve)

• Lesions of the brain preventing the establishment of good vision (for example, cortical visual impairment)

• Patients diagnosed with photosensitive epilepsy

• Patients diagnosed with or suspected of having conjunctivitis

• Loss of suppression at filter 4 or less as measured with the Sbisa bar

• Establishment of normal vision by refractive adaptation (wearing glasses after presentation)

• Inability to comply with the follow-up visits required

• Refusal to accept randomisation

• Have participated in a previous study examining I-BiT™ treatment

### Study procedures

#### Screening and eligibility assessments

Potential participants will be identified by various methods including identification by members of the clinical team or by contacts made through the website and via posters in clinic. Informed consent will be obtained and eligibility assessed.

### Baseline assessments

A full orthoptic assessment a maximum of 1 month prior to the start of the study must be available/performed. This assessment must include:

• Uniocular assessment of visual acuity with a LogMAR test (aided with glasses if applicable)

• Cover test (with and without glasses if applicable)

• Ocular motility

• Assessment of binocular functions

• Visuscope assessment

• Sbisa bar (if applicable)

### Randomisation and codebreaking

Subject numbers will be assigned sequentially as each subject enters the study. The subjects will be assigned to a study treatment arm through an independently-developed web-based randomisation system. Randomisation will be performed after eligibility has been checked prior to first treatment, and will be equal and stratified according to whether the patient has had previous treatment for their amblyopia. The research orthoptist will be the only member of the study team who will have knowledge of the randomised treatment.

### Subsequent assessments

Patients will receive their randomised treatment for 30 min each week for 6 weeks. In addition to their baseline assessment, they will have assessments at the following visits, all performed by an independent assessor.

### Week 1 (pre-treatment)

Uniocular assessment of visual acuity with a LogMAR test (aided with glasses if applicable) prior to first treatment.

### Week 3 (mid-treatment)

Uniocular assessment of visual acuity with a LogMAR test (aided with glasses if applicable) after third treatment.

If at this visit, visual acuity in the amblyopic eye has regressed by 0.1 LogMAR units or more, then the participants should be withdrawn from the study.

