### Statistical methods

The primary endpoint is considered confirmatory with secondary endpoints considered supportive.

The primary analyses will be performed on the intention-to-treat (ITT) population. Supportive analyses may be performed on a per protocol (PP) population defined prior to code-break.

Except where a patient has been withdrawn from the study or otherwise documented, all missing data will be assumed to be missing completely at random (MCAR). The primary analyses will not use any imputation methods to compensate for missing data.

There will be two primary comparisons: I-BiT™ games *vs.* non-I-BiT™ games and I-BiT™ DVD *vs.* I-BiT™ games. Both these analyses will comprise ANCOVA using baseline visual acuity as a co-variate, where distributional assumptions are met. If these assumptions are not met, a suitable transformation will be applied or a non-parametric method used. There will be no correction for multiplicity.

Summary statistics including mean, median, SD and 95% confidence intervals will be provided, in addition to appropriate graphical displays.

All datasets will be defined in a blinded manner prior to database lock.

Further details of the statistical analyses will be provided in the statistical analysis plan which will be finalised prior to database lock.

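### Withdrawing children who regress at week 3 leaves the no-imputation ITT analysis of week-6 acuity with only children selected on their earlier acuity

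*Protocol article*

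**What the plan says.** All references are to the protocol article.

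- **Week 3 (mid-treatment):** if "visual acuity in the amblyopic eye has regressed by 0.1 LogMAR units or more, then the participants should be withdrawn from the study". The text says the study, not the treatment, and no section provides for acuity assessment after withdrawal.
- **Primary outcome:** "The primary endpoint is the change from baseline to the end of treatment (6 weeks) in visual acuity". This is measured after the week-3 decision.
- **Statistical methods, population:** "The primary analyses will be performed on the intention-to-treat (ITT) population".
- **Statistical methods, model:** "Both these analyses will comprise ANCOVA using baseline visual acuity as a co-variate". Week-3 acuity is not in the stated model.
- **Statistical methods, missing data:** "Except where a patient has been withdrawn from the study or otherwise documented, all missing data will be assumed". The mechanism assumed there is MCAR (missing completely at random). The next sentence reads: "The primary analyses will not use any imputation methods to compensate for missing data".
- **Sample size:** "25 patients per arm would be required to detect a minimum difference of 0.2 LogMAR units", giving 75 in total.
- **Trial status:** "21 patients have been randomised" as of 6 November 2012.

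**The concern.** The protocol itself creates the missing primary data, by a rule that depends on the outcome. A child who is 0.1 LogMAR worse at week 3 (four letters of 0.025) is removed three weeks before the primary measurement. Acuity at weeks 3 and 6 will be correlated, so those removed are on average the children who would have done worst at week 6.

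Two consequences follow. First, the mean gain among the remaining children exceeds the mean gain among those randomised, in every arm. Second, if one arm is already doing better at week 3, fewer of its children are removed. The worse arm is then flattered more, and the difference between arms is pulled toward zero. The comparison of I-BiT game with non-I-BiT game is the one chiefly exposed. The risk is a missed or understated effect, not a false positive. Game against DVD is little affected if those two arms behave alike.

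**Working it through.** **1. The plan's own figure.** With SD 0.25, difference 0.20, two-sided 5% and 80% power, the normal formula gives n = 2 × (1.960 + 0.842)² × 0.25² / 0.20² = 24.5, so 25 per arm. This reproduces the plan. Exact t-test power at 25 per arm is 79.1%; 26 per arm would be needed for 80%. The total is 3 × 25 = 75, so there is no allowance for loss. Lost numbers alone, with no bias, would give 73.6% at 22 per arm and 69.3% at 20.

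**2. Following one child through the rules.** Regressed at week 3, so withdrawn; withdrawn, so no week-6 acuity; no week-6 acuity and no imputation, so not in the ANCOVA. The MCAR sentence sets withdrawn children apart but gives no other handling for them. LOCF appears in the abbreviation list and is not specified as a method anywhere in the article.

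**3. Size of the selection effect.** The documents give neither a withdrawal rate nor the correlation between visits, so the following are assumptions:
- Changes are normal, with improvement positive, and are rounded to one letter.
- The true week-6 difference is 0.20 and the week-3 difference is 0.10.
- The correlation ρ between week-3 and week-6 change is 0.7.

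Rounding to 0.025 puts the effective cut at −0.1 + 0.0125 = −0.0875. For an arm with week-3 mean m₃ and SD s₃, and week-6 mean m₆ and SD s₆:
- z = (−0.0875 − m₃)/s₃
- proportion withdrawn = Φ(z)
- mean among those remaining = m₆ + ρ·s₆·φ(z)/(1 − Φ(z))

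Scenario 1 (SD 0.25 at both visits, control change 0):
- Control: z = −0.35, withdrawn 36%, remaining mean 0 + 0.7 × 0.25 × 0.589 = 0.103.
- Active: z = −0.75, withdrawn 23%, remaining mean 0.20 + 0.7 × 0.25 × 0.389 = 0.268.
- Difference: 0.268 − 0.103 = 0.165, against a true 0.20.

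A control arm that truly does not change appears to gain 0.10. About 16 control and 19 active children are analysed. At correlations of 0.5 and 0.8 the difference is 0.175 and 0.160.

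The same formula gives the other differences. Power is from simulated trials of 25 per arm, using a two-sample t-test on change.

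| Scenario | SD wk 3 / wk 6 | Control change wk 3 / wk 6 | Withdrawn, control vs active | Expected difference | Power |
|---|---|---|---|---|---|
| 1 | 0.25 / 0.25 | 0 / 0 | 36% vs 23% | 0.165 | 57% |
| 2 | 0.25 / 0.25 | 0.05 / 0.10 | 29% vs 17% | 0.169 | 63% |
| 3 | 0.143 / 0.25 | 0 / 0 | 27% vs 10% | 0.153 | 55% |
| 4 | 0.143 / 0.143 | 0 / 0 | 27% vs 10% | 0.173 | 98% |
| 5 | 0.10 / 0.143 | 0.05 / 0.10 | 8% vs 1% | 0.185 | 99% |
| 6, arms separate only after week 3 | 0.25 / 0.25 | 0 / 0 | equal | 0.200 | 71-72% |

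With full follow-up at SD 0.25, power is 79%. The value 0.143 is the SD of change in the shutter-glasses pilot described in the Background.

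**4. Null case.** With identical arms the withdrawal is equal and the difference is 0.000. Simulated type I error is 4.8-5.3%.

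**The case against.** The strongest reply is that the damage may be small and is in the safe direction. How often the trigger fires is unknown. Scenario 1 needs 36% of control children to lose four letters in three weeks. The Sample size section does not say whether 0.25 is the SD of acuity or of change, and the only SD of change in the document is 0.143. In that pilot all nine completers improved. With SDs of that order, power stays at 98-99% and the estimate is 0.173-0.185. The power figures also come from a t-test; ANCOVA on baseline would usually do somewhat better. All of this stands, and it limits the size of the problem without removing it.

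A second reply is that the analysis plan may deal with withdrawals. It can add sensitivity analyses, and a repeated-measures likelihood model that includes week 3 would be a sensible one. But the primary method is already fixed here. Under the rule no child below the cut has a week-6 value, so any such model must extrapolate into a range with no data. An analysis plan cannot recover acuity that was not measured.

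A third reply is that the rule protects children aged 4 to 8. Stopping treatment on deterioration is reasonable and is not criticised. Ending follow-up adds nothing to that protection.

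Finally, the remedy may not raise power, because children whose treatment is stopped may lose benefit. That is correct, and its cost is set out with the fix.

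**Conclusion.** The concern holds and should be fixed. The week-3 rule, the week-6 endpoint and the no-imputation ANCOVA together make the stated ITT analysis a complete-case analysis selected on an interim value of the outcome. That follows from the text and needs no assumption about rates.

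The size does depend on assumptions. If half of a true 0.20 difference is present by week 3, and the correlation is 0.7, the expected estimate is 0.153-0.185. Power is 55-63% at a week-6 SD of 0.25 and 98-99% at 0.143. If the arms separate only after week 3 there is no bias, only lost numbers. If they do not differ at all, type I error is unaffected. A positive result would therefore not be undermined by this rule; a null or small result would be hard to interpret, and the gains reported within each arm would be too large.

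**What to change.** Amend the Week 3 section so that regression of 0.1 LogMAR or more stops study treatment only. Keep the masked week-6 and week-10 acuity assessments for these children, and include their week-6 values in the existing primary ANCOVA. State that the comparison is a treatment-policy one: acuity at week 6 whether or not treatment was stopped. For week-6 values still missing, one likelihood-based repeated-measures sensitivity analysis including week-3 acuity is a useful addition, but it is secondary.

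The cost is a short amendment. The visits are already scheduled, and 75 − 21 = 54 children would be covered from entry, going by the stated trial status.

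The downside is interpretive: acuity after stopping may reflect lost treatment or the start of standard care, and the report must say so. The change restores an unselected comparison but does not guarantee 80% power. In scenario 1, with 23% of active children stopped:
- If stopping costs them nothing, the difference is 0.200 and power is 79%.
- If they lose half of the 0.20 gain, the difference is 0.20 − 0.227 × 0.10 = 0.177 and power is about 65%.
- If they lose all of it, the difference is 0.20 − 0.227 × 0.20 = 0.155 and power is 49%, below the 57% of the present analysis.

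Even in the last case the figure is the effect of the assigned treatment in all randomised children, which is what an ITT analysis is meant to estimate.
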